#### Non-randomized, treatment-as-usual (TAU) group

It is possible that medication and CBT will produce similar therapeutic responses in our patient population. We would like to be able to estimate the effect of each treatment and each treatment sequence in our SMART design against usual treatment in real-world settings. Therefore, we will include a non-randomized TAU group consisting of patients who satisfy all study eligibility criteria, pass the 3-level screen, an decline participation in the randomized trial, but who consent to participate in a truncated study measurement sequence. In addition to the eligibility measures for these patients, we will acquire a small subset of measures (SCARED-41, CAIS, CBCL, treatment expectations, ADIS Supplemental Service Form) at the same time points as in the randomized group – at baseline and weeks 6, 12, 18, and 24, as well as the quarterly follow-up assessments thereafter.

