Patient-Identified Treatment Needs	Youth Top Problems [90]	C	All	6	69–.88	3	B,12,24,Q
Well-Being	PROMIS Purpose & Meaning Short Form [91]	C,P	All	8	.90–.98	1	B,12,24,Q
Life Satisfaction	NIH Toolbox Life Satisfaction [92]	C,P	3–17	5	.86–.97	3	B,12,24,Q
Self-Efficacy	NIH Toolbox Self-Efficacy [93]	C,P	7–17	10	.90–.92	3	B,12,24,Q
Family Functioning	Family Assessment Device [94]	C,P	12+	12	.69–.84	5	B,12,24,Q
Social Functioning	NIH Toolbox Social Relations & Loneliness [92]	C	7–17	29	.95	10	B,12,24,Q
School Functioning	Grade point average	Report card	N/A	N/A	N/A	N/A	B,12,24,Q
	School attendance	Report card	N/A	N/A	N/A	N/A	B,12,24,Q
	Student Subjective Wellbeing Questionnaire	C	7–17	16	.92	4	B,12,24,Q
Sleep	Sleep Self Report [95]	C	7–12	26	.76	7	B,12,24,Q
	Children’s Sleep Habits Questionnaire [96]	P	4–10	23	.68–.78	7	B,12,24,Q
Emotion Regulation	Brief Version of the Difficulties in Emotion Regulation Scale (DERS-16) [97, 98]	C	11–17	16	.92	2	B,12,24,Q
Coping with Change	Anxiety Control Questionnaire for Children [99, 100]	C	8–18	10	.89	2	B,12,24,Q
Comorbid Psychiatric Symptoms	Child Behavior Checklist [101] Youth Self-Report [102]	C,P	6–17 11–17	83 112	.78–.97 .71–.95	12	B,12,24,Q
	Mood and Feelings Questionnaire [103]	C,P	All	13		5	B,12,24,Q
Side Effects	The Pediatric Side-Effect Checklist	C,P,Cl	All	24	.78	5	B,6,12,18,24,Q
Suicidal Ideation	Columbia-Suicide Severity Rating Scale [104]	C	All	6	.73–.93	2	B,12,24,Q
Family’s Accommodation of Patient’s Symptoms	Family Accommodation Scale-Anxiety [105]	P	All	13	.82–.90	3	B,12,24,Q
Treatment Expectations	Treatment Expectancies [106]	C,P,Cl	All	3	N/A	2	B,M
Service Use	Anxiety Disorders Interview Schedule For DSM-5 (ADIS), the supplemental service form (SSF) [107]	P	All	5	N/A	5	B,12,24,Q
Treatment Preferences	Treatment Acceptability and Preferences [108]	C,P	All	2	.88	5	B,12
Clinician Relatedness & Therapeutic Alliance	Outcome Rating Scale and Session Rating Scale [109]	C,P,Cl	All	8	.87–.96 & .88	1	B,M
Anxious Avoidance	Child Avoidance Measure [110]	C,P	8–18	8	.86–.91	3	B,M,Q
Parent Anxiety & Depression Symptoms	PHQ9 & GAD7 [111, 112]	P	All	16	0.83–0.92 ([111, 112])	3	B,12,24

C=Child-report; P=Parent-report; Cl = Clinician-report

B=Baseline; 6 = Week 6; 12 = Week 12; 18 = Week 18; 24 = Week 24; Q = Quarterly Follow-up; M = Monthly, every 4 weeks during the 24-week trial

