#### Retention

These efforts will begin with informed consent. Developing a trusting personal relationship with the family is vitally important for study adherence and ongoing participation, and the treatment provided during the study will help to build those relationships. We will strive to assign a specific research assistant to each patient for the duration of participation. If study appointments are missed, the family will be contacted and the visit promptly rescheduled. If unable to reach them during regular business hours, we will attempt contact at varying days and hours. Cards and small presents will be provided on holidays and birthdays. We will collect comprehensive tracking and location information, including home and work addresses, email addresses, social media contacts, Medicaid and social security numbers of parents and participants, and phone numbers of relatives and others with close relationships with the family. We will conduct quick monthly check-ins with all participants (e.g., text message, social media direct message) to foster our relationship and ensure contact information is current; participants will receive $5 for each check-in completed. When not found at their last-known residence, staff will review change-of-address reports and contact next-of-kin or participant-identified friends. We will keep a record of clinics attended by our participants and, as necessary and with permission, use the clinics to maintain contact. We will compensate participants appropriately in the randomized trial for each research assessment, escalating compensation with time after the lengthier baseline visit to encourage continuing participation ($25 for baseline, $5 for week 6, $20 for week 12, $5 for week 18, $65 for week 24 assessments, $5.00 for each monthly check-in, and $20 for each of the quarterly follow-ups after the 24-week trial). Participants in the non-randomized (TAU) cohort will received $5 for their assessments at each time point.

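### The TAU group consists of families who declined randomization and is not given the treatment-preference scale, so the contrast with usual care is liable to confounding that can be adjusted for only indirectly

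*Protocol article*

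**What the plan says.** All references are to the protocol article.

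- **Purpose.** The section on the non-randomized TAU group starts from the possibility that medication and CBT perform alike. It then states: "We would like to be able to estimate the effect of each treatment and each treatment sequence in our SMART design against usual treatment".
- **Who is in it.** The article describes a "non-randomized TAU group consisting of patients who satisfy all study eligibility criteria, pass the 3-level screen, an decline participation in the randomized trial", provided that they consent to a shortened set of measurements.
- **What is collected.** Beyond the eligibility measures, TAU families give a "small subset of measures (SCARED-41, CAIS, CBCL, treatment expectations, ADIS Supplemental Service Form"), at baseline, weeks 6, 12, 18 and 24, and quarterly afterwards.
- **What is not on that list.** Table 2 includes an instrument called "Treatment Acceptability and Preferences": child and parent report, 2 items, 5 minutes, at baseline and week 12. Treatment expectancies is a separate Table 2 instrument of 3 items, and it is on the TAU list.
- **Why preference matters.** The section on gaps in evidence says that modality decisions are influenced by the wish to keep a child off medication and by stigma. It adds that minority families often have an aversion to medication yet tend to see CBT as less feasible, which limits adherence.

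**The concern.** The benchmark group is defined by a refusal. If treatment preference is one reason families refuse, and preference also bears on adherence and hence on outcome, TAU and randomized children may differ at week 24 for reasons unrelated to the treatment received. The usual partial remedy is to measure the suspected confounder in both groups and adjust for it. Here it is measured on one side only.

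A statistical analysis plan cannot repair this later, because a covariate never collected in TAU cannot enter a model. Apart from TAU, every comparison in the trial is between active treatments. If Main Effect 1 is null, readers will be drawn to the TAU contrast to judge whether either treatment beats usual care, and the section carries no caution about reading it that way.

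**Working it through.** **1. Is preference captured in TAU by another route?**

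| Source in the protocol article | What TAU families supply | Preference scored? |
|---|---|---|
| TAU section | SCARED-41, CAIS, CBCL, treatment expectations, ADIS service form | No; expectations is a related construct |
| Screening, stage 3 | KSADS-COMP, Child Trauma Screen, C-SSRS, CAIS, patient profile (medical, treatment, demographic) | No |
| Recruitment | Expectations and preferences are to be explored with families | Not said to be scored or kept for those who decline |
| Recruitment, participants versus non-participants | Demographics and screening measures | No |

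Preference is therefore not directly measured in TAU by any listed instrument. Expectations, severity, impairment, diagnoses, demographics and service use are available.

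**2. How large could the bias be?** The article gives no TAU sample size, effect size, power or expected prognostic gap, so there is no figure of its own to reproduce. The values below are assumptions that show a range.

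- d = difference in mean preference between decliners and participants, in SD: 0.2, 0.5 or 0.8.
- b = shift in outcome per SD of preference, in SD: 0.1, 0.2 or 0.3.
- Bias without adjustment = d × b.

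| d | b = 0.1 | b = 0.2 | b = 0.3 |
|---|---|---|---|
| 0.2 | 0.02 | 0.04 | 0.06 |
| 0.5 | 0.05 | 0.10 | 0.15 |
| 0.8 | 0.08 | 0.16 | 0.24 |

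**3. How much can the proxy remove?** Suppose expectations correlates r with preference and differs between the groups only through preference. Adjusting for it then leaves d × b × (1 − r²).

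- r = 0.3: 0.3² = 0.09, so 9% is removed. The largest bias falls from 0.24 to 0.24 × 0.91 = 0.218 SD.
- r = 0.6: 0.6² = 0.36, so 36% is removed. The largest bias falls from 0.24 to 0.24 × 0.64 = 0.154 SD.

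For scale, the sample-size section gives 0.31 SD as the smallest Main Effect 1 detectable with 80% power. Under these assumptions the bias runs from negligible to a substantial fraction of that. The proxy helps, but leaves most of it in place.

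**The case against.** The strongest reply is that this comparison is peripheral and openly labelled. The group is called non-randomized and its purpose is worded as a wish. TAU appears in none of the specific aims, the hypotheses, the comparators, the sample-size section or the main analysis models. This stands: no randomized result depends on TAU, and the point is modest in rank.

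Four stronger readings are tempting, and the documents do not support them.

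- **That the contrast is confounded by something that cannot be adjusted for.** Expectations is a partial proxy, and several prognostic measures are shared. The article also does not rule out that preferences explored at recruitment are recorded. Families may refuse for other reasons that it mentions: worry about receiving the less effective treatment, or seeing randomization as unfair. What can be said is that the contrast is liable to confounding, with preference one plausible source.
- **That a false-positive rate can be attached to the omission.** With 162 completers in a Stage 1 arm (324/2), an assumed 100 TAU children and SE = √(1/100 + 1/162) = 0.127 SD, a treatment no better than usual care would be declared different in 12%, 35% or 66% of trials at prognostic gaps of 0.1, 0.2 or 0.3 SD. Both the TAU size and the gap are assumed, and the figures would fit any non-randomized comparison. They do not measure the effect of leaving out this scale.
- **That payment will produce differential completion.** TAU families receive $5 per time point, against $65 at week 24 in the trial. But both groups receive $5 at weeks 6 and 18, and the randomized battery is listed at 93 child and 78 parent minutes, whereas TAU completes a short subset. The effect on retention is unknown.
- **That the plan compares TAU with non-remitters alone, or lacks an adjustment model.** The article describes no such comparison. The choice of model may properly sit in an analysis plan that is not shown.

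**Conclusion.** The point holds as a limited one. The article sets out to "estimate the effect of each treatment and each treatment sequence in our SMART design against usual treatment in real-world settings", using a group defined by refusal of randomization, and does not collect there the preference scale that it collects from randomized families. Its own background makes preference a credible confounder, and with the listed measures only indirect adjustment is possible.

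Size and direction are unknown. The range of 0.02 to 0.24 SD before adjustment rests entirely on assumed values of d and b, and the share a proxy could remove (9% to 36%) on assumed correlations. The randomized tests of Main Effects 1 and 2 and their interaction are untouched. Collecting preference would reduce the problem but not remove it, because accepting or refusing randomization still separates the groups completely.

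**What to change.** Make two changes in the TAU section.

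1. Add the existing 2-item acceptability and preference scale, child and parent versions, to the TAU baseline assessment. This has to happen while TAU enrolment is open, since baseline preference cannot be recovered afterwards.
2. Reword the purpose. Suggested text: the TAU contrast is an exploratory, observational comparison, adjusted for baseline measures shared with the randomized sample, including treatment preference; because TAU families declined randomization, it cannot by itself establish the efficacy of either treatment if Main Effect 1 is null.

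The cost is about 5 minutes at one TAU assessment, going by the time listed in Table 2, and a softer claim. The randomized design, sample size and primary analyses do not change.

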#### Screening

We anticipate screening 80% of newly registered and current patients (ages 8–17) for anxiety disorders at our 9 study sites. We will employ a 3-stage screening process. In Stage 1 Screening, we will administer the 5-item version of the parent and child SCARED [86, 136, 137] to patients presenting to any of our outpatient services at all our performance sites. A cut-off score ≥ 3 discriminates “anxiety” from “non-anxiety” patients with 74% sensitivity and 73% specificity [86] and has demonstrated utility to screen youth at risk for anxiety across primary care settings [138]. We will regard a score of ≥3 on either the parent or child SCARED-5 as a positive screen. The screener will request permission from the parent to allow the clinic to share the parent contact information with our study team if the child screens positive for anxiety. In Stage 2 Screening, youth who screen positive on either the parent or child 5-item SCARED will complete the 41-item SCARED. Those who score ≥ 25 [139, 140] on the total score for the parent or child SCARED will undergo further characterization for study eligibility and possible recruitment. In Stage 3 Screening, youth and their parents who pass Stage 2 screening will be administered several additional assessments to complete determination of study eligibility. These will include the clinician-administered KSADS-COMP (for diagnoses of anxiety disorders and OCD), Child Trauma Screen (for PTSD), Columbia-Suicide Severity Rating Scale, CAIS (for functional impairment), and a patient profile (for medical illnesses, treatment, and demographic information).

#### Recruitment

For patients satisfying all eligibility criteria, a study coordinator will contact the parent and patient, describe the study (including randomization requirements), address questions, and, if the parent and patient agree to participate, schedule a baseline assessment and initial clinical visit. Formal written consent and assent will be obtained in person in a private area or online, over the telephone, or by mail at the baseline assessment. When consenting in person is not an option, we will consent over the phone or video conference.

We will attend carefully to elements of study design and execution that enhance recruitment. Participants are often concerned about being randomized to a less effective treatment [141, 142], but here the 2 treatment arms will be in true clinical equipoise [143]. Patients will not face the possibility of being randomized to an ineffective or minimally effective treatment. This was important to the parents in our community engagement activities, who enthusiastically supported our proposed SMART design. Outcomes will be patient-centered [141], in many cases the study will be presented by their primary clinician [141, 144, 145], treatment expectations and preferences will be explored [146], informed consent will be presented simply, confidently [147], and in lay language [141, 142, 144, 145], most clinic/study visits will be scheduled after school or on weekends [144, 148], study demands will be kept to a minimum [141, 142], and patients and parents will not be blind to treatment assignment [141, 142, 145]. A large majority of participants will have Medi-Cal insurance, which does not require co-payments, so participation should not entail a financial burden [149]. We will employ the principles of QuinteT Recruitment Intervention methods, which comprise in-depth, real-time investigation of recruitment obstacles, participation, attendance, and motivation, followed by implementation of tailored strategies to address identified challenges across all treatment arms as the trial proceeds [143, 150]. We will record demographics and screening measures of all screened patients to compare those who do and do not choose to participate, to assess the representativeness of our study sample. We estimate an attrition of 20% over the 24-week RCT, yielding 323 treatment completers. If attrition proves higher, we will increase numbers recruited to ensure we achieve at least that number of completers. Our patient numbers, clinician staffing, and research coordinator burden will readily support this increased recruitment.

#### Retention

These efforts will begin with informed consent. Developing a trusting personal relationship with the family is vitally important for study adherence and ongoing participation, and the treatment provided during the study will help to build those relationships. We will strive to assign a specific research assistant to each patient for the duration of participation. If study appointments are missed, the family will be contacted and the visit promptly rescheduled. If unable to reach them during regular business hours, we will attempt contact at varying days and hours. Cards and small presents will be provided on holidays and birthdays. We will collect comprehensive tracking and location information, including home and work addresses, email addresses, social media contacts, Medicaid and social security numbers of parents and participants, and phone numbers of relatives and others with close relationships with the family. We will conduct quick monthly check-ins with all participants (e.g., text message, social media direct message) to foster our relationship and ensure contact information is current; participants will receive $5 for each check-in completed. When not found at their last-known residence, staff will review change-of-address reports and contact next-of-kin or participant-identified friends. We will keep a record of clinics attended by our participants and, as necessary and with permission, use the clinics to maintain contact. We will compensate participants appropriately in the randomized trial for each research assessment, escalating compensation with time after the lengthier baseline visit to encourage continuing participation ($25 for baseline, $5 for week 6, $20 for week 12, $5 for week 18, $65 for week 24 assessments, $5.00 for each monthly check-in, and $20 for each of the quarterly follow-ups after the 24-week trial). Participants in the non-randomized (TAU) cohort will received $5 for their assessments at each time point.

### Community and stakeholder engagement

One of our core values is community engagement. We are committed to ensuring that patients, caregivers, clinicians, and other healthcare stakeholders play a meaningful role throughout the entire research process. We see our patients and other healthcare stakeholders as equitable partners—not simply as research subjects—and we plan to leverage their lived experiences and expertise to ensure this research is patient centered, relevant, and ultimately useful. Their values, priorities, and preferences are of paramount importance, and so they have been full partners in developing this study design and in selecting its measures.

#### Our community partners

This research will be conducted in Los Angeles County, which is more populous than 42 states and more racially/ethnically, linguistically, culturally, religiously, and socioeconomically diverse than any other city or county in the world. We have deep expertise conducting culturally tailored community engagement that fully embraces this diversity, and in conducting research in partnership with underserved, under-represented, and high disparity populations. We define *patient partners* as including teenagers (≥ age 12 years); parents, guardians, caregivers; parent advocacy/support groups; and local, state, and national organizations and advocacy groups (e.g., National Alliance on Mental Health, with a California chapter and local chapters throughout Los Angeles). We define *stakeholder partners* as including pediatricians and community primary care physicians, hospitals, health/mental health systems, teachers and educators; purchasers, and policy makers (including local health-related foundations).

#### Leveraging our Southern California Clinical and Translational Science Institute (SC CTSI)

We will leverage the resources, services, and infrastructure available through our SC CTSI and its Community Engagement (CE) Program. The CTSI was created to engage vulnerable communities in clinical and translational research; facilitate academic-community partnerships to ensure patient and community engagement in research; and develop, evaluate, and disseminate novel approaches to engaging diverse populations in research. The SC CTSI will offer a range of resources to this project, including access to community health workers who have deep roots and expertise working in Latino (*promotoras)*, African American (*Cultural Brokers)*, and Asian American communities.

#### Community engagement to inform study design and methods

We conducted extensive engagement activities with patients, parents, and caregivers, healthcare providers, and other stakeholder groups, to ensure our research incorporates their voice and reflects their interests in a meaningful way. These activities were conducted in both English and Spanish, in safe spaces (churches, schools, libraries, community health centers) located in East, South, and Central Los Angeles. A brief description of these engagement activities, and important feedback obtained during each, follows:
A.Community Listening Sessions. We hosted a well-attended Community Listening Session focused on pediatric anxiety, during which parents shared their experiences and discussed the challenges associated with raising a child or adolescent with an anxiety disorder. Parents told us how they would want to be involved in this study and offered considerable input as to how we might collectively disseminate research findings to ensure uptake by patients and other stakeholders.B.Our Community/Our Health Los Angeles (OC/OH-LA). OC/OH-LA is a CTSI community engagement strategy to foster ongoing conversation between health researchers and community members. We hosted an OC/OH-LA session, which was attended by 45 parents, grandparents, and mental health community workers from South L.A. We provided an overview of pediatric anxiety and approaches to evidence-based treatment, followed by questions and discussion. Parents discussed the shame that youth with a mental health condition feel, the secrecy they keep, and how this shame/stigma creates a significant barrier to accessing treatment services. Parents also expressed their fears, misperceptions, and general lack of awareness of the safety, efficacy, and long-term effects of medications to treat anxiety. This feedback deeply informed our planned recruitment and retention efforts. Moreover, it suggests that our dissemination efforts targeted to consumers of care will need to address, head-on, both stigma and fear of medication if our goal to encourage uptake of the study findings is to be achieved.C.Focus Groups with Parents and Teenagers to Identify Patient-Centered Outcomes. We conducted focus groups with parents/caregivers and, separately, teenagers living with anxiety, referred from mental health service organizations. Parents and their teenage children identified outcomes that concerned them most, as listed in “*Patient Centered Outcomes*” **(**Table 2**)**. They also echoed the OC/OH-LA session, calling for outreach efforts to address stigma and medication concerns. This feedback drove decisions about study outcomes and the scales used to assess them.D.Research 101. Another SC CTSI community engagement activity is a *Research 101* training manual and curriculum entitled, “Engaging Communities in Research, the Fundamentals of Research,” which presents the fundamentals of research, the importance of increasing diversity in research, and potential myths and barriers to participation. We offered Research 101 to a group of parents and caretakers. In general, we heard that parents have many fears and misperceptions about research and the intentions of researchers. Parents also expressed concern about randomization as potentially “unfair” if treatment is withheld. Following Research 101, parents demonstrated increased knowledge about research, study methods, and designs. Parents also appreciated and understood how, in our proposed study, treatment will not be withheld but rather randomization will occur to evaluate the effectiveness of two gold-standard treatment modalities; they were highly supportive of this design, suggesting that we offer Research 101 to our Parent Advisory Council members (described below) and an abbreviated version of Research 101 to parents of our participants before beginning the study, to help them understand and feel more comfortable with their child’s participation. We believe this will also improve participant retention. We will include information about research methods in our dissemination materials (e.g., newsletters, brief summary reports) throughout the study and at its conclusion to encourage uptake of study findings.E.Engaging Mental Health Providers & Mental Health Support and Advocacy Groups. We met with mental health support and advocacy organizations to solicit suggestions about study design and our approach to engagement. Participants included the Director of the County’s Department of Mental Health and the President of NAMI California. Other organizations that we have begun to engage and will continue to work with include: the American Academy of Child and Adolescent Psychiatry; National Federation of Families for Children’s Mental Health; Mental Health America; Anxiety and Depression Association of America; United Advocates for Children and Families; California Mental Health Advocates for Children and Youth; Los Angeles Unified School District; Pacific Clinics; Young Minds Advocacy; and our study’s partner sites. We will also work with 2 youth-focused organizations: (1) International Children’s Advisory Network (iCAN), a worldwide consortium of children’s advisory groups known as Kids Impacting Disease through Science (KIDS); and (2) Young Person’s Advisory Groups (YPAGS), youth groups working to provide a voice for children and families in research. These organizations will help us develop our own KIDS and YPAGS for this project. Also, we will partner with WeRiseLA; this organization seeks to use art and community-building to transform the mental health care system and to foster mental health and wellbeing as a civil right.
